## Abstract

Previous clinical trials for drug-susceptible tuberculosis (DS-TB) have shown that first-line treatment with doses of rifampicin up to 40 mg/kg are safe and increase the early treatment response for young adults with pulmonary tuberculosis. This may lead to a shorter treatment duration for those persons with TB and a good baseline prognosis, or increased treatment success for vulnerable subgroups (age > 60, diabetes, malnutrition, HIV, hepatitis B or hepatitis C coinfection, TB meningitis, stable chronic liver diseases). Here, we describe the design of a phase 2b/c clinical study under the hypothesis that rifampicin at 35 mg/kg is as safe for these vulnerable groups as for the participants included in previous clinical trials. RIAlta is an interventional, open-label, multicenter, prospective clinical study with matched historical controls comparing the standard DS-TB treatment (isoniazid, pyrazinamide, and ethambutol) with rifampicin at 35 mg/kg (HR^35^ZE group) vs. rifampicin at 10 mg/kg (historical HR^10^ZE group). The primary outcome is the incidence of grade ≥ 3 Adverse Events or Severe Adverse Events. A total of 134 participants will be prospectively included, and compared with historical matched controls with at least a 1:1 proportion. This will provide a power of 80% to detect non-inferiority with a margin of 8%. This study will provide important information for subgroups of patients that are more vulnerable to TB bad outcomes and/or treatment toxicity. Despite limitations such as non-randomized design and the use of historical controls, the results of this trial may inform the design of future more inclusive clinical trials, and improve the management of tuberculosis in subgroups of patients for whom scientific evidence is still scarce. Trial registration: EudraCT 2020-003146-36, NCT04768231.

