### 2.5. Recruitment

Participants will be prospectively included and compared with historical controls from the same sites. Participants meeting all the inclusion and not any of the exclusion criteria will be offered to start on the HR^35^ZE arm. After 8 weeks, participants will be managed according to the national TB guidelines.

The selected retrospective participants will provide a comparison for the primary safety outcome, and to the secondary efficacy outcome of culture conversion at 8 weeks using MGIT media. 

We adhered to all Pockock’s principles for historical controls except for the use of information from participants that were previously randomized in clinical trials [23]. To avoid the selection bias that may arise because of this limitation, we aim to include all adult patients fulfilling the inclusion criteria treated with HR^10^ZE in the participating sites between January 2017 and December 2019 (to avoid the influence of the 2020–2021 SARS-CoV-2 pandemic in TB diagnoses and follow-up). Thus, the records of all patients from that period with pulmonary and extrapulmonary rifampicin susceptible tuberculosis will be reviewed. We will capture the severe or grade 3 adverse events and week 8 microbiological status from those who are ≥60 years, or ≥18 years and have a diagnosis of diabetes, malnutrition, HIV, HBV or HCV coinfection, other stable chronic liver diseases, or TB meningitis, and have no pharmacological immunosuppression. We intend to control the retrospective cohort to match the prospective one for age, sex, cavitation in lung TB, and severity in TB meningitis. In case not enough matched controls are not found, we will extend the search with patients until the calculated sample size in the control arm is achieved. The historical cohort will include participants from only Spain, Portugal, and Paraguay and not likely from the Netherlands, as optimized doses of rifampicin have been used in both Dutch sites for more than a decade in the same participant subgroups as included in our study.

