### 2.8. Assessment of Study Outcomes, Analysis Groups, and Duration of Follow-Up

The primary safety hypothesis is that the incidence of adverse events in the high dose rifampicin (35 mg/kg) supplemented with isoniazid, pyrazinamide, and ethambutol [HR^35^ZE] during the first 8 weeks of treatment will not exceed that of controls on a standard HRZE regimen (rifampicin 10 mg/kg) [HR^10^ZE]. The HR^35^ZE regimen will be considered unsafe if in a non-inferiority analysis, the upper limit of the 95% confidence interval of the difference of proportions in grade ≥ 3 AE (according to CTCAE scale version 5) between the experimental and the historical control arm exceeds 8%. The most common adverse events related to therapy with higher rifampicin doses were vomiting, headache, hyperuricemia, pain in the extremities, and pruritus. No significant differences according to rifampicin dose (from 10 to 35 mg/kg) were found in a recent systematic review and in a retrospective study collecting the real-life experience from a Dutch center [24,25].

To assess the AE and ensure a homogeneous evaluation of their grade, severity, expectedness, and treatment relatedness, we will administer a standardized training for the investigators from all different sites. In addition, both for the prospective and the retrospective cohorts, grade 3 or higher adverse events and SAE will be reviewed by the trial’s Steering Committee for relatedness classification. When no consensus is reached, the Data and Safety Monitoring Board formed by experts independent from the trial will make the final decision.

Tolerability will be measured as any adverse event (grade 1 to 4), treatment dropout rate, and any dose reduction. For efficacy outcome, the hypothesis is that in DS-TB participants (pulmonary disease), the proportion of participants experiencing successful treatment outcomes (culture and smear negative) at the end of the intensive phase of treatment on HR^35^ZE will be non-inferior to that of controls on HR^10^ZE. The HR^35^ZE regimen will be considered ineffective if the lower limit of the 95% CI of the proportion of participants with a negative sputum culture (sputum sterilization), or unable to produce sputum if they have a previous negative culture at week 8, is more than 10% lower than that of historical controls treated with HR^10^ZE. Other exploratory outcomes will be reported descriptively. 

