### 2.9. Sample Size Assumptions and Justification

For the sample size calculation, a non-inferiority design is assumed and the upper limit of the 95% confidence interval (CI) of the difference of proportions in grade 3 or higher adverse events at 8 percentage points has been set. We assume that 5% of patients will not be assessable. Alpha risk is set in 0.1 and power in 0.8. Based on the previous literature and our previous experience, expected standard treatment grade ≥ 3 AE are 5–10% (mean 8%) among experimental arms and standard treatment arms. Considering this, the number of participants per arm has been calculated to be 134 participants. Because of the limited recruitment capacity for this trial, we could not target specific numbers of participants for each sub-group of risk factors. 

Based on a feasibility survey performed at the planning stage, the target enrollment rates per country were: Paraguay 6.25 participants per month; Spain, Portugal, and the Netherlands 1.6 participants per month.

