### 2.10. Main Outcomes Analysis

The primary safety outcome will be analyzed as the proportion of participants in the HR^35^ZE and historical HR^10^ZE groups that received at least one dose of treatment with an unfavorable outcome after 8 weeks of experimental treatment start. According to the clinical and laboratory information, participants will be classified as having an unfavorable outcome if they suffered one or more grade ≥ 3 AE or SAE that are possibly, probably, or definitely related to rifampicin OR they did not complete their treatment because of other reasons OR were lost-to follow-up. High doses of rifampicin will be considered non-inferior to standard doses if the upper boundary of the 95% CI of the proportion of participants with an unfavorable outcome is less than 8% that of the point estimate in the historical standard dose group.

Efficacy will be assessed as the proportion of participants with pulmonary TB in the HR^35^ZE and the historical HR^10^ZE groups that have sputum culture conversion in liquid media at week 8. The unfavorable efficacy outcome will be defined as having a positive sputum culture at week 8.

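### The primary rule is stated as a plain difference between arm proportions, which loses the balance from matching if the number of controls per participant differs across the matching factors

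*Protocol article*

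**What the plan says.** All references are to the protocol article.

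**How controls are obtained.** The Abstract says participants will be "compared with historical matched controls with at least a 1:1 proportion", with no upper limit. Section 2.5 gives three further statements:

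- on the source, "we aim to include all adult patients fulfilling the inclusion criteria" who received standard-dose treatment at the sites in 2017–2019;
- on matching, "We intend to control the retrospective cohort to match the prospective one for age, sex, cavitation in lung TB, and severity in TB meningitis";
- on a shortfall, "we will extend the search with patients until the calculated sample size in the control arm is achieved", without repeating that these additional patients must match.

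**How the arms are compared.** Section 2.8 uses "the upper limit of the 95% confidence interval of the difference of proportions in grade ≥ 3 AE" between the experimental and historical arms, with 8% as the limit. Section 2.9 sizes the trial on "the difference of proportions in grade 3 or higher adverse events at 8 percentage points has been set". Section 2.10 asks whether "the upper boundary of the 95% CI of the proportion of participants with an unfavorable outcome is less than 8"% relative to the point estimate in the historical group.

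None of these sections carries the matching factors into the estimate. There is no mention of sets, weights, strata or standardisation.

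**The concern.** The comparison is not randomised, and section 2.15 itself calls the design especially prone to bias. Matching on four factors is one of the main safeguards. It protects a crude difference in proportions only if the controls end up with the same distribution of those factors as the participants.

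The recruitment plan does not secure that. Keeping all eligible patients, leaving the ratio open above 1:1, and adding patients when matches run short are each ways in which some kinds of participant get more controls than others. The crude control proportion then over-represents the kinds of patient who were plentiful in 2017–2019.

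If those patients are at low risk of grade 3 or higher events, high-dose rifampicin looks worse than it is. If they are at high risk, it looks safer than it is. The second direction matters more, because it can produce a non-inferiority conclusion on safety that the data do not support.

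**Working it through.** **1. The plan's own figure.** Section 2.9 gives a margin of 8 points, 5% not assessable, expected rates of 5–10% in both arms, and "Alpha risk is set in 0.1 and power in 0.8". The usual formula for two independent proportions with no true difference is

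n per arm = 2p(1 − p)(z₁₋α + z₀.₈)² / 0.08².

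With p = 0.10 and one-sided α = 0.1: 2 × 0.09 × (1.2816 + 0.8416)² / 0.0064 = 126.8, so 127, and 127 / 0.95 = 133.7, so 134. This matches the stated number. The stated mean of 8% gives 104, or 110 after the 5% allowance, so it does not match. The 134 is therefore reproduced by a calculation that treats the arms as unmatched. That describes the planning and does not prove what the analysis will be.

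**2. Bias of the crude difference.** The documents give no risks by matching factor and no ratios by type of patient. The following are assumptions for illustration:

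- half of the 134 participants (67) are in a low-risk stratum and half in a high-risk stratum;
- there is no treatment effect;
- k_L and k_H controls are taken per participant in the two strata.

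Crude control rate = (k_L × r_L + k_H × r_H) / (k_L + k_H).

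| Risks (low, high) | k_L : k_H | Participants | Crude controls | Crude difference |
|---|---|---|---|---|
| 4%, 12% | 1 : 1 | 8.0% | 8.0% | 0 |
| 4%, 12% | 3 : 1 | 8.0% | (12 + 12)/4 = 6.0% | +2.0 points |
| 4%, 12% | 1 : 3 | 8.0% | (4 + 36)/4 = 10.0% | −2.0 points |
| 5%, 10% | 3 : 1 | 7.5% | (15 + 10)/4 = 6.25% | +1.25 points |
| 5%, 10% | 1 : 3 | 7.5% | (5 + 30)/4 = 8.75% | −1.25 points |

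The standardised estimate averages the stratum differences with the participants' weights: ½ × 0 + ½ × 0 = 0 in every row.

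**3. Effect on the decision.** Normal approximation, 134 participants and 67 × 4 = 268 controls. The probability of declaring non-inferiority is Φ[(0.08 − 1.96 × SE used − expected difference) / true SE].

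*True excess equal to the margin* (8 points added in each stratum), risks 4% and 12%, ratio 1:3. The crude difference is expected at 16% − 10% = 6 points.

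- SE used = √(0.16 × 0.84/134 + 0.10 × 0.90/268) = 0.0366.
- True SE, allowing for the strata = 0.0364.
- (0.08 − 0.0717 − 0.06)/0.0364 = −1.42, a probability of 7.8%, against 2.5% for the standardised analysis.

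At 3:1 the crude rule gives 0.5%. With risks of 5% and 10% the same calculation gives 5.3% at 1:3 and 1.0% at 3:1.

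*No true effect*, risks 4% and 12%. At 3:1 the crude rule declares non-inferiority in 58.7% of trials, against 72.5% when standardised. At 1:3 the figures are 92.1% and 80.2%.

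**4. The interval itself.** For 1:1 pairs the correct SE is the independent-samples SE times √(1 − ρ). Strata of 4% and 12% imply ρ = 0.04² / (0.08 × 0.92) = 0.022. At 8% risk and 134 per arm, the independent half-width is 6.50 points, and 6.43 points allowing for ρ = 0.02. The difference is about 1%, on the conservative side.

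**The case against.** The strongest reply is that the documents do not say what the concern needs. A reader might infer that the plan fixes an analysis of pooled, independent proportions on individually matched sets with a varying ratio. It does not. Sections 2.8 to 2.10 fix an effect measure and a margin and name no estimator or CI method. A weighted or standardised difference would satisfy the wording of section 2.8. Section 2.5 describes matching the cohort as a whole, which reads at least as well as frequency matching. The ratio may be constant, and the detail may be in an analysis plan that is not shown. All of this stands.

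It does not dispose of the point. Frequency matching protects the crude difference only if controls are sampled to the participants' distribution, and keeping every eligible patient or adding patients to reach a number does not ensure that. Nothing in the Abstract or section 2.5 promises a constant ratio. Section 2.10 refers to a single point estimate for the historical group. Followed as written, the recruitment plan and the decision rule do not fit together.

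A reader might also infer that an interval ignoring the pairing is materially wrong. It is not: at 1:1 the effect is about 1% under the assumed strata, and conservative.

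Finally, the strata are chosen values. The imbalance is aligned fully with risk, and the study of 1149 patients cited in the Introduction found no association between age over 60 and adverse reactions. The bias could well be smaller than shown.

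**Conclusion.** The point holds as a conditional one. If control numbers per participant differ across age, sex, cavitation or meningitis severity, and those factors carry risk, the stated comparison is biased, whether matching is individual or by frequency. With a constant ratio, or controls sampled to the participants' distribution, it is not.

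On the assumed strata the bias is 1.25 to 2 points, about one sixth to one quarter of the margin, in either direction. In the unfavourable direction, the chance of declaring non-inferiority at a true 8-point excess rises from 2.5% to between 5.3% and 7.8%. These figures rest on assumed risks and ratios and show scale only. The error concerns the point estimate, not the width of the interval.

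The estimator should be changed or clarified before the control data are analysed. The point does not show that the plan has committed to a wrong analysis.

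**What to change.** State in the analysis plan whether matching is individual or by frequency, and whether the ratio is fixed or variable. Then define the primary estimate to fit:

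- **Frequency matching, or all eligible controls kept:** a risk difference standardised to the participants' distribution of age group, sex, cavitation and meningitis severity, in categories coarse enough that each contains controls.
- **Individual sets:** each control weighted by 1 / (number of controls in its set).

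Compute the 95% CI for that estimator, apply the 8-point rule to its upper limit, and report the crude difference descriptively. State that controls added through the extended search enter on the same terms.

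Keep to the stated matching factors. With about 0.08 × 127 ≈ 10 events per arm, a model with several further covariates would be fragile.

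The cost is wording and a little more analysis work, since the matching factors must be collected anyway. Unequal weights can widen the interval: in the 4% and 12% example with no true effect, the half-width goes from 5.4 to 6.1 points at 3:1, and from 5.8 to 5.6 at 1:3.

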### 2.2. Objectives and Endpoints

The study primary objective is to evaluate the safety of high-dose rifampicin (35 mg/kg/d) as part of a standard first line regimen using standard doses of isoniazid (5 mg/kg), pyrazinamide (25 mg/kg), and ethambutol (15–25 mg/kg) for 8 weeks in adult subjects with pulmonary or extrapulmonary DS-TB belonging to difficult to treat subgroups. The secondary objectives are to evaluate the tolerability, efficacy, bactericidal activity, pharmacokinetic/pharmacodynamics, and cost effectiveness of high dose rifampicin, among others. 

The primary safety endpoint is the proportion of participants and historical controls with one or more grade 3 or higher adverse events (AE) according to the CTCAE v5 or SAE at 8-weeks after treatment with high-dose rifampicin onset. Table 2 below describes in detail the analysis population and primary safety outcomes. The secondary tolerability endpoint includes the proportion of participants with any AE. The secondary efficacy endpoint includes the proportion of participants and historical controls who have sputum culture conversion at 8 weeks after treatment onset or a proportion of participants with clinical improvement according to the treating physician (if follow-up images are available for extra-pulmonary TB) but without a follow up sample at 8 weeks after treatment onset.

Most TB phase 2 trials complete their intervention at week 8 or earlier and then participant care is transferred to a public institution within the National TB programs, so the information about end of treatment and post-treatment outcomes is scarce [10,17,18]. In the RIAlta trial, after the intervention and the primary safety objective evaluation, an extended follow-up period will be offered to participants, in line with the phase 2b/c design suggested by Phillips et al. [19]. This will provide information about end-of-treatment outcomes and relapse incidence in the prospective group.

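### The central review shared by both cohorts checks relatedness but not CTCAE grade, although grade 3 or higher is the main route to the primary endpoint

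*Protocol article*

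**What the plan says.** Section 2.8 gives two measures for consistent event assessment.

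- **Training.** To "ensure a homogeneous evaluation of their grade, severity, expectedness, and treatment relatedness, we will administer a standardized training for the investigators from all different sites".
- **Central review.** This covers the patients treated prospectively and the historical controls alike. Its scope is stated as follows: "grade 3 or higher adverse events and SAE will be reviewed by the trial’s Steering Committee for relatedness classification". The tie-break follows: "When no consensus is reached, the Data and Safety Monitoring Board formed by experts independent from the trial will make the final decision".

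The review therefore has a stated purpose (relatedness) and a stated entry condition (already graded 3 or higher, or serious).

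The primary endpoint is worded in several places.

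- Section 2.2 counts patients "with one or more grade 3 or higher adverse events (AE) according to the CTCAE v5 or SAE", with no relatedness condition.
- The decision rule in section 2.8 uses the "difference of proportions in grade ≥ 3 AE (according to CTCAE scale version 5"), and section 2.9 sizes the trial on the same quantity. Neither mentions SAEs or relatedness.
- Section 2.10 requires relatedness to rifampicin, and also counts non-completion for other reasons and loss to follow-up.

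For controls, section 2.5 says: "We will capture the severe or grade 3 adverse events and week 8 microbiological status". The source is the records of patients treated between January 2017 and December 2019. The Discussion concedes that this information was not gathered systematically, that grade 1–2 events are usually absent or incomplete in clinical records, and that the adverse-event guidelines are harmonised for the prospective part.

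**The concern.** Only the committee review applies one set of assessors to both cohorts. It checks an attribute that only the section 2.10 wording uses. The attribute that decides the section 2.8 rule is not centrally confirmed. Because entry requires grade 3 or seriousness, a non-serious event recorded as grade 2 is not seen by the committee at all.

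The conditions of grading differ by cohort, and cohort is the treatment comparison. Prospective grades are given in an open-label setting under harmonised guidelines. Control grades depend on what routine notes from years earlier happen to contain. Training can make today's investigators more alike, but it cannot add detail to those notes. A modest difference in how the grade 2/3 boundary is applied would pass straight into the risk difference. It could make an equally safe regimen look worse, or hide a real excess. Without a common grading step, the size and direction could not be recovered afterwards.

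The point concerns the grade of recorded events. Whether events were recorded at all is a separate matter.

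**Working it through.** **1. Which attribute each wording uses**

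| Place | Grade ≥3 | SAE of any grade | Relatedness | Other routes |
|---|---|---|---|---|
| Abstract; section 2.2; Discussion | yes | yes | no | no |
| Section 2.8 decision rule | yes | no | no | no |
| Section 2.9 sample size | yes | no | no | no |
| Section 2.10 analysis | yes | yes | yes | non-completion, loss to follow-up |
| Section 2.8 central review | entry condition only | entry condition only | **reviewed** | – |

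Grade appears in every wording and is the only criterion in two of them. Relatedness appears in one.

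**2. The plan's own figure**

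Inputs from section 2.9: margin 8 points, alpha 0.1 (sidedness not stated), power 0.8, event rate 5–10% (mean 8%) in both arms, 5% not assessable.

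n = (z₁₋α + z₁₋β)² × 2p(1−p) / margin²

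With one-sided alpha 0.10 and p = 10%: (1.2816 + 0.8416)² × 0.18 / 0.0064 = 126.8, so 127 evaluable; 127/0.95 = 133.7, so 134 per arm. This matches the plan. (The stated mean of 8% gives 104, inflated to 110. That is a separate matter.) I use 127 evaluable per arm below.

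**3. Size of a grading shift (assumption)**

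The documents give no misgrading rate. Assume that 15–25% of patients have a recorded grade 2 event and that 10% of these are read one grade higher in one cohort only:

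0.15 × 0.10 = 1.5 points; 0.25 × 0.10 = 2.5 points.

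That is 1.5/8 = 19% to 2.5/8 = 31% of the margin. Patients already counted for another grade 3 event would not move, so the shift would be somewhat smaller where events overlap.

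**4. Effect on the section 2.8 rule**

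Exact enumeration over two binomials with n = 127 each. Non-inferiority is met when d + 1.96 × √[p₁(1−p₁)/127 + p₀(1−p₀)/127] < 0.08, where p₁ and p₀ are the observed proportions and d = p₁ − p₀.

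| True rates (HR35ZE v control) | Read as | Chance of meeting the margin |
|---|---|---|
| 8% v 8% | 8% v 8% | 66% |
| 8% v 8% | 9.5% v 8% | 46% |
| 8% v 8% | 10.5% v 8% | 34% |
| 8% v 8% | 8% v 9.5% | 77% |
| 8% v 8% | 8% v 10.5% | 83% |
| 16% v 8% | 16% v 8% | 2.9% (false) |
| 16% v 8% | 16% v 9.5% | 6.1% (false) |
| 16% v 8% | 16% v 10.5% | 9.2% (false) |

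A normal approximation agrees closely for the first row: SE = √(2 × 0.08 × 0.92/127) = 0.0340; Φ(0.08/0.0340 − 1.96) = 65%.

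The 66% starting point lies below the planned 80% because the rule uses a 95% interval while the sample size uses alpha 0.1. Grading does not cause that gap. Only the movement from 66% belongs to this point.

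**The case against.** The strongest reply is that grading is not neglected. Section 2.8 names grade first among the attributes the training is meant to make homogeneous, and one scale, CTCAE v5, is fixed. Who grades the historical events, and by what rule, is detail that an article may leave to the full protocol. The review does serve the section 2.10 definition, which requires relatedness. The weakness of historical controls is also disclosed: section 2.15 acknowledges susceptibility to bias and says the results should inform future designs. All of this stands, and it limits the point. It does not remove it, because the article is not silent on the review: it states the purpose and the entry condition, and neither covers grade.

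A reader might infer more than the documents support:

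- **That the endpoint turns on grade alone.** SAEs count whatever their grade in the abstract, section 2.2, section 2.10 and the Discussion, and section 2.10 adds non-completion and loss to follow-up.
- **That no event graded 2 ever reaches the committee.** A serious one does, since SAEs are sent.
- **That chart abstractors grade the control events.** The article does not say who does.
- **That the common events are all graded by judgment.** The list in section 2.8 includes hyperuricemia, a laboratory finding.
- **That the bias runs against HR35ZE.** Nothing in the documents fixes its direction.
- **That every recorded grade 2 event should be sent for review.** The Discussion says such events are mostly missing or incomplete in clinical records, and section 2.5 captures only severe or grade 3 events in controls. Upgrading would therefore fall mainly on HR35ZE and add bias.

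**Conclusion.** The point holds in a limited form. The review common to both cohorts is restricted to the relatedness of events already graded 3 or higher or serious, while the section 2.8 rule and the section 2.9 sample size rest on grade. Training is the only stated safeguard for grade, and it cannot standardise what was written in 2017–2019.

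Under an assumed shift of 1.5 to 2.5 points, the chance of meeting the margin with a true 8% in both arms moves by roughly 20 to 32 points downward (66% to 46–34%) or 11 to 17 points upward (66% to 77–83%). With a true excess equal to the margin, false non-inferiority rises from 2.9% to 6–9% if controls are read higher. These figures depend on the assumed misgrading rates, 127 evaluable per arm and a Wald 95% limit. They show what a plausible shift would do and do not estimate one that will occur. This is a worthwhile, inexpensive improvement to make before event review begins; it does not invalidate the design.

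**What to change.** In section 2.8, widen the stated purpose of the Steering Committee review from relatedness to CTCAE v5 grade and relatedness, for the events already sent to it from both cohorts. In addition:

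1. Derive laboratory-based grades in both cohorts by one program from the recorded values, whatever grade the site assigned. This can correct laboratory grades in both directions.
2. Use the reviewed grade in the primary analysis and the site-assigned grade as a sensitivity analysis.
3. Keep any review of grade 2 clinical events as a sensitivity analysis only, because these events are largely unrecorded in controls.

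**Cost.** Modest extra committee time and one grading program. The committee, the review of both cohorts and the tie-break already exist, and no patient procedures are added.

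**Limitation.** For non-serious clinical events, a review confined to those already graded 3 or higher can only lower grades and cannot recover under-graded events. The comparison with site grades would show how much was lowered in each cohort. Reviewed control grades also remain only as good as the notes behind them.

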## 2. Methods

### 2.1. Study Design

This is an interventional, open-label, multi-center, historically matched controlled prospective clinical study of high dose rifampicin (35 mg/kg, HR^35^ZE group) versus standard-dose (10 mg/kg/day, historical HR^10^ZE group) in a vulnerable population. Clinical trials with rifampicin are typically open label as the drug causes orange discoloration of the urine and other body fluids that makes it difficult to maintain blinding for participants and investigators [15,16,17]. Table 1 shows a comparative of key design aspects in different phase 2 studies using high-dose rifampicin in the last 15 years.

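### Section 2.10 makes rifampicin-relatedness decide which events count in the primary outcome, sections 2.2, 2.8 and 2.9 do not, and no masking is stated for the committee that judges it

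*Protocol article*

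**What the plan says.** Section 2.2 of the protocol article gives its primary safety endpoint in these words: "proportion of participants and historical controls with one or more grade 3 or higher adverse events (AE) according to the CTCAE v5 or SAE". Assessment is 8 weeks after treatment start. Causality plays no part in it. The decision rule in section 2.8 and the sample size in section 2.9 also refer to grade 3 or higher events and an 8-point margin without a relatedness condition.

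Section 2.10 classes a participant as unfavourable after "one or more grade ≥ 3 AE or SAE that are possibly, probably, or definitely related to rifampicin". Two further routes need no causal judgment: "they did not complete their treatment because of other reasons OR were lost-to follow-up".

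Section 2.8 says which events are judged: "both for the prospective and the retrospective cohorts, grade 3 or higher adverse events and SAE will be reviewed". Responsibility lies with the trial's "Steering Committee for relatedness classification". The section adds standardized training for investigators at all sites and a fallback: "When no consensus is reached, the Data and Safety Monitoring Board formed by experts independent from the trial will make the final decision".

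Section 2.1 calls the trial an "interventional, open-label, multi-center, historically matched controlled prospective clinical study". The Discussion confirms that every prospective participant is assigned to 35 mg/kg. The article does not say whether cohort, dose, site or date is hidden from the committee or the board.

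**The concern.** Under section 2.10 a severe event enters the primary outcome only after someone decides that it was "possibly, probably, or definitely related to rifampicin". Cohort and dose coincide, so an assessor who knows the cohort knows the dose while deciding whether the drug caused the event.

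That knowledge could act in either direction. Awareness of 35 mg/kg could make attribution more likely in the HR35ZE group and hide true non-inferiority. The trial's working hypothesis that the dose is safe could make attribution less likely and produce a false claim of non-inferiority. Either way the error goes straight into the risk difference that is compared with 8 points, and few events are expected.

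**Working it through.** **Inputs from the article.** Margin 8 percentage points on the upper 95% confidence limit (sections 2.8 and 2.9); expected event rate 5–10%, mean 8%, in both arms; 5% not assessable; alpha 0.1; power 0.8; 134 per arm (section 2.9).

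**The plan's own figure.** With 10% in both arms and one-sided alpha 0.10, n = (1.2816 + 0.8416)² × 2 × 0.10 × 0.90 / 0.08² = 126.8, so 127; 127 / 0.95 = 133.7, so 134. The figure reproduces on those inputs. (At the stated mean of 8% the same formula gives 104, inflated to 110. That mismatch is a separate matter.) I use 127 assessable per arm below.

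**How many events decide the result.** Upper limit = p₁ − p₀ + 1.96 × √[p₁(1 − p₁)/127 + p₀(1 − p₀)/127], event component only.

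| Control events | HR35ZE events | Difference | Standard error | Upper limit | Below 8 points? |
|---|---|---|---|---|---|
| 10 (7.9%) | 11 (8.7%) | 0.8 | 3.46 | 7.6 | yes |
| 10 (7.9%) | 12 (9.4%) | 1.6 | 3.53 | 8.5 | no |
| 13 (10.2%) | 13 (10.2%) | 0.0 | 3.80 | 7.5 | yes |
| 13 (10.2%) | 14 (11.0%) | 0.8 | 3.87 | 8.4 | no |

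This step needs no assumption about attribution: close to the threshold, one relatedness call changes the conclusion. A one-sided 95% limit allows one more HR35ZE event in each case.

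**Differential attribution.** The article gives no attribution rate, so these are assumptions: any-cause rate 10% in both arms, and 80% of events judged related where attribution is undisturbed. Counted rate = any-cause rate × share judged related. The probability of meeting the 8-point rule comes from exact binomial enumeration.

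| Share judged related, HR35ZE / control | Counted rates | Chance of non-inferiority |
|---|---|---|
| 80% / 80% | 8% / 8% | 66% |
| 80% / 70% | 8% / 7% | 58% |
| 80% / 60% | 8% / 6% | 48% |
| 70% / 80% | 7% / 8% | 78% |
| 60% / 80% | 6% / 8% | 88% |

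Now take true any-cause rates of 20% and 10%. Equal 80% attribution gives 16% against 8%, exactly at the margin.

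| Share judged related, HR35ZE / control | Counted rates | Chance of false non-inferiority |
|---|---|---|
| 80% / 80% | 16% / 8% | 3% |
| 70% / 80% | 14% / 8% | 8% |
| 60% / 80% | 12% / 8% | 20% |

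A 5-point gap does less: 62% or 72% instead of 66%, and 5% instead of 3%.

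**The case against.** The strongest objection is that this is a condensed article, which presents itself as a summary of the protocol. What an adjudicating committee is shown often stands in the full protocol or a charter, and the open-label label is explained by the difficulty of blinding participants and investigators. A reader might infer that the committee will know each patient's dose. The article does not support that; it supports only that no masking is stated. The point still stands in conditional form, because the article does describe the adjudication (who, which cohorts, how disagreement is settled) and masking is not among the safeguards listed.

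Those safeguards count. Training, one committee for both cohorts and an independent board all help. But the board acts only without consensus, and a leaning shared by the committee produces consensus.

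Relatedness may also not be the intended condition, since only section 2.10 imposes it. If the any-cause wording prevails, this route to bias closes. That is why reconciliation comes first in the fix.

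The size is illustrative. The threshold of possible relatedness is low and both cohorts take rifampicin, so a 20-point gap may be too wide. The calculation also leaves out non-completion and loss to follow-up, which count without a causal judgment. Adding an assumed 5% for these lowers the 66% to 49% and the 20% to 16%.

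Finally, section 2.15 concedes that the design is prone to bias and limits the results to informing later trials. That lowers the consequence, but it names non-randomization and historical controls, not attribution.

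**Conclusion.** The point holds in conditional form. The primary outcome is defined with a relatedness condition in section 2.10 and without one in sections 2.2, 2.8 and 2.9. If section 2.10 governs and the review is unmasked, differential attribution can move the AE and serious-event component of the primary result in either direction.

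The event-count result rests only on 127 per arm and a 95% Wald interval. The ranges of 48–88% for showing non-inferiority, and of 8–20% (against 3%) for false non-inferiority at the margin, also rest on assumed any-cause rates and assumed gaps of 10 to 20 points from 80%. They show sensitivity and do not predict bias. The documents do not show that attribution will differ, or in which direction.

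**What to change.** 1. Reconcile sections 2.2, 2.8, 2.9 and 2.10, so that one definition states whether relatedness is required.
2. Report the any-cause comparison of grade 3 or higher AEs or serious events, with the same 8-point margin, alongside the related-event analysis. This is nearly free and does not depend on masking.
3. Where relatedness is used, have the Steering Committee, and the monitoring board for unresolved cases, classify events from standard-format summaries in mixed order, with cohort, rifampicin dose, site or country, and calendar dates removed. Site matters because section 2.5 expects no Dutch controls, so a Dutch case would reveal the cohort. Set this before review begins.

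The cost is staff time to redact all grade 3 or higher events and serious events, not only those later judged related: about 13 patients per arm at an assumed 10% any-cause rate (0.10 × 127 = 12.7). No further assessor is needed. Masking will be imperfect, since sparse routine records may reveal the cohort, and it does not correct differences in how events were ascertained in the historical records.
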